### Interventions

The control group intervention protocol was designed in accordance with the 2015 Chinese Guidelines for the Diagnosis and Treatment of Sudden Deafness [15]. These guidelines were developed based on extensive RCT data from multicenter clinical studies on sudden deafness in China, incorporating updates from the latest American and German clinical guidelines as well as recent research advancements, ensuring alignment with clinical practice in China [1,4,16]. The treatment regimen for the control group was designed to comprehensively address the inflammation and microcirculatory disturbances associated with ISSNHL through a combination of prednisone, Ginkgo biloba extract, and batroxobin injection. The specific pharmacological interventions are detailed in Table 2.

**Table 2 table2:** Standard treatment regimen for the control group.

Period	Drug	Dosage and administration	Duration
Weeks 1-2 after onset	Prednisone (glucocorticoid)	1 mg/kg/day (maximum 60 mg), oral, once daily in the morning	5 days
Weeks 1-2 after onset	Ginkgo biloba extract	87.5 mg in 250 mL 5% glucose, intravenous infusion, once daily	2 weeks
Weeks 1-2 after onset	Batroxobin injection	5 batroxobin units in 250 mL 5% glucose, intravenous infusion, every other day^a^	2 weeks
Weeks 3-4 after onset	Ginkgo biloba tablets	9.6 mg × 2 tablets, oral, 3 times daily	2 weeks

^a^Before the administration of batroxobin, blood tests are required to confirm fibrinogen levels (>1.5 g/L) and normal coagulation parameters (eg, prothrombin time or activated partial thromboplastin time). Fibrinogen and coagulation function are monitored 24 hours after the first dose and periodically thereafter.

Patients in the EA group will receive the same treatment as the control group, in addition to EA, which will not interfere with their medication treatment.

The EA group received acupuncture using disposable sterile needles (Hwato Needles; Suzhou Medical Appliance Factory) at acupoints previously identified in studies as functionally related to ISSNHL and tinnitus, including Tinggong (SI19), Tinghui (GB2), Yifeng (SJ17), Yunting area, Anmian, Waiguan (SJ5), Zhongzhu (SJ3), Taichong (LR3), and Taixi (KI3). For limb acupoints, 30-gauge needles (0.25 mm in diameter, 40 mm long) will be inserted to a depth of 10-15 mm. For head acupoints, 32-gauge needles (0.25 mm in diameter, 25 mm long) will be inserted to a depth of 3 mm. A specialized acupuncture technique will be used when needling the Tinggong point (SI19) on the impacted side. The patient will be instructed to slightly open their mouth, and a needle (0.25 mm in diameter, 40 mm long) will be inserted to a depth of approximately 15-25 mm. The assistant will pinch the patient’s nostrils, prompting the patient to take a deep breath, close their mouth, and hold their breath to push air through the Eustachian tube into both ears. During this procedure, the acupuncturist will gently twist the needle until the patient feels a local sensation of soreness or distension. Afterward, the patient will exhale through the mouth, and the acupuncturist will withdraw the needle by approximately 10 mm and leave it in place. Additionally, the Tinghui (GB2) and Yifeng (SJ17) points on the impacted side will be needled and connected to an EA device (KWD-808I type; Great Wall, Yingdi). A sparse wave with a frequency of 2-15 Hz will be applied at an intensity that induces muscle contraction and is tolerable for the patient. The needles will be retained for 30 minutes. Figure 2 provides an operational illustration of the acupuncture technique at the Tinggong (SI19) point, while Figure 3 shows the acupuncture point selection diagram. EA treatment will last for a total of 4 weeks, with 4 sessions per week during the first 2 weeks and 3 sessions per week during the last 2 weeks, conducted every other day.

**Figure 2 figure2:**
[figure not shown]
The operational illustration of acupuncture technique at SI19.

**Figure 3 figure3:**
[figure not shown]
The acupuncture point selection diagram.

### Outcome Measures

#### Feasibility Primary Outcomes

The feasibility primary outcomes are recruitment rate, defined as the proportion of enrolled participants relative to the target sample size; adherence rate, measured as the proportion of participants completing at least 80% of the prescribed EA sessions over 4 weeks, as extracted from treatment logs; data completeness, assessed as the proportion of participants with fully collected baseline and follow-up data for key measures such as PTA and Tinnitus Handicap Inventory (THI); and safety outcomes, recorded as the incidence of adverse events during the treatment period, based on session-by-session reports [31,32].

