**Assessments**																			
	**Feasibility outcomes**																		
		Recruitment rate		N/A		N/A		N/A		N/A		✓		N/A		N/A			
		Adherence rate		N/A		N/A		N/A		N/A		✓		N/A		N/A			
		Data completeness		N/A		N/A		N/A		N/A		✓		N/A		N/A			
		Adverse events		N/A		N/A		✓		✓		✓		✓		✓			

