### Sample Size

As previous RCTs have not investigated EA as a combination intervention in patients with ISSNHL with tinnitus, it is challenging to determine the optimal sample size through power calculation. Therefore, rather than performing a formal sample size estimation, this trial will adopt a preliminary exploratory clinical pilot design to estimate the appropriate sample size [28]. However, to preliminarily assess the feasibility of the proposed intervention, we will ensure an adequate number of participants in our experimental design by adhering to the established guideline of a minimum of 12 participants per group for pilot studies [29]. A previous study suggested that each group should have a sample size ranging from 20 to 25 cases for exploratory clinical trials assessing the effectiveness of intervention measures [30]. Therefore, in this study, each group will consist of 25 patients, resulting in a total of 50 cases across the 2 groups. To account for a potential dropout rate of 20%, we will recruit a total of 60 patients (30 per group). The results of this study will provide effect size data for calculating sample sizes in future large-scale RCTs.

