As a pilot study, the primary feasibility outcomes include the proportion of enrolled participants relative to the target sample size (recruitment rate, reported as a percentage), the proportion of participants completing at least 80% of prescribed EA sessions over 4 weeks (adherence rate, extracted from treatment logs and reported as a percentage), the proportion of participants with complete baseline and follow-up data for key measures such as PTA and THI (data completeness, reported as a percentage, with the proportion of missing data reported as a complementary indicator), and the incidence of adverse events during the treatment period (safety outcomes, recorded from session-by-session reports and summarized as total events and incidence rate per 100 person-sessions). These feasibility outcomes will be presented using descriptive statistics, without hypothesis testing.

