## Results

This study began recruitment on July 15, 2024, and is scheduled to conclude on August 31, 2025. To date, 42 participants have been enrolled, with 35 having completed the intervention and posttreatment assessments (control group: n=21; EA group: n=14). Following protocol publication, data compilation and analysis will be conducted, with results anticipated to be published in a relevant journal in 2026.

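### Recruitment rate is defined as enrolled over target, which gives neither an uptake fraction nor an accrual rate, and Table 1 scores data completeness at t3 although its definition needs t4 and t5

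*Protocol article*

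**What the plan says.** - **Recruitment rate.** Outcome Measures, Feasibility Primary Outcomes, names "recruitment rate, defined as the proportion of enrolled participants relative to the target sample size". Statistical Analysis repeats the same ratio: "the proportion of enrolled participants relative to the target sample size (recruitment rate, reported as a percentage". Neither place gives a screened, eligible or approached denominator, or a unit of time.
- **Target.** Sample Size states that "each group will consist of 25 patients, resulting in a total of 50 cases across the 2 groups", then raises this to 60 (30 per group) for an assumed 20% dropout.
- **Progress and calendar.** Results reports: "To date, 42 participants have been enrolled, with 35 having completed the intervention and posttreatment assessments". Recruitment began on 15 July 2024. The Abstract and Results have the study concluding on 31 August 2025; Design and Setting has it continuing until December 2025.
- **Data completeness.** Feasibility Primary Outcomes defines it as "the proportion of participants with fully collected baseline and follow-up data for key measures", with pure tone audiometry (PTA) and the Tinnitus Handicap Inventory (THI) as examples. No last visit is named. In Table 1 the row "Data completeness" has one tick, at t3 (1 month after treatment), and is not applicable at t4 and t5. The same table schedules PTA and THI at t0 to t5, and Statistical Analysis uses all six of those time points.

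**The concern.** The trial is a pilot whose declared purpose is to inform the design and sample size of a larger multicentre trial. For that, recruitment has to answer two questions: what fraction of the patients seen can be randomized, and how fast does each centre accrue? Eligibility is narrow (flat audiogram, onset within one week, no medication or acupuncture in the past six months), so both answers matter here. Enrolled over target answers neither. It measures progress towards a quota.

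The completeness issue is of a different kind. The text defines a measure over all follow-up, while the schedule scores it before the last two follow-ups take place. Anyone who follows the table would report retention for treatment plus one month, and that figure could be carried into the larger trial as if it covered the full three months after treatment.

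**Working it through.** **Inputs.** Evaluable number 50, dropout allowance 20% and target 60 (Sample Size); 42 enrolled (Results); start date 15 July 2024 and two end dates (Abstract, Results, Design and Setting); visits t1 to t5 (Design and Setting, Table 1). The article gives no screening count and no date for the 42, so both are varied as assumptions.

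**1. The plan's own target.** 50 × 1.20 = 60, which reproduces the stated figure.

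**2. The ratio to date.** 42/60 = 70%.

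**3. What the ratio cannot distinguish.** If the target is filled, 60/60 = 100% for any number screened, S. The share randomized is 60/S. For assumed values of S:
- S = 75: 60/75 = 80%
- S = 120: 60/120 = 50%
- S = 300: 60/300 = 20%

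The defined outcome is 100% in all three.

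**4. Whether it must reach 100%.** Assume constant accrual, with enrolment capped at 60.

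*If the 42 were reached by the publication date, 14 May 2025:* 303 days, about 9.95 months, so 42/9.95 ≈ 4.2 per month.
- Enrolment open to 31 August 2025 (412 days): 42 × 412/303 = 57.1, or 57.1/60 ≈ 95%.
- 31 August 2025 as the last t5 visit: enrolment closes 28 + 91 = 119 days earlier, on 4 May 2025. The projection is 40.6, already passed by the actual 42, so the ratio stays near 70%.
- Enrolment open to 31 December 2025 (534 days): 42 × 534/303 = 74.0, capped at 60, or 100%.

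*If the 42 were reached by 28 February 2025:* 228 days, about 5.6 per month. The three results become 75.9 (capped, 100%), 54.0 (90%) and 98.4 (capped, 100%).

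So the reported value runs from about 70% to 100% according to which end date applies, whether it closes enrolment or follow-up, and when the 42 were reached.

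**5. Position of the tick in Table 1.** The header has seven columns: t–1, then t0 to t5. The completeness row reads four not-applicable entries, a tick, then two not-applicable entries. The tick is in the fifth column, t3. Other rows support this alignment: adverse events are ticked at t1 to t5 and PTA at t0 to t5. Scoring at t3 covers three of five follow-ups (t1, t2, t3).

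**6. Size of the completeness difference.** Assume that loss is spread evenly (constant retention p per follow-up) and that dropout is the only source of missing data. If total loss by t5 is L, then p = (1 − L)^(1/5), and completeness through t3 is p³.

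| L by t5 | Through t3 | Through t5 | Difference (points) |
|---|---|---|---|
| 10% | 93.9% | 90% | 3.9 |
| 20% (the protocol's allowance) | 87.5% | 80% | 7.5 |
| 30% | 80.7% | 70% | 10.7 |

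**The case against.** **On recruitment.** A reader might infer that the ratio is 100% by construction. The article does not support that: nowhere does it say that recruitment continues until 60 are enrolled. It gives calendar ends, the ratio stands at 70%, and a shortfall would itself say something about feasibility. Accrual could also be calculated from enrolment dates, since the start date is given and randomization is stratified by centre. The enrolment flowchart, which is not shown, may track screening numbers. All of this stands. It does not change the fact that a named primary outcome is explicitly defined, twice, as a quantity that uses none of this information. Because the definition is stated rather than left open, it is not a detail deferred to a fuller document.

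**On completeness.** The text definition is not limited to t3, Statistical Analysis adds the proportion of missing data as a complementary indicator, and PTA and THI are collected through t5. Recruitment, adherence and completeness all carry a single tick at t3, so the tick may mark when summaries are compiled rather than which visits count. That reading is plausible, and it confines the defect to the table. It does not remove it, because a measure requiring full follow-up data cannot be compiled before t4 and t5 have occurred.

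A reader might also infer that neither measure can inform the larger trial, or that the omitted visits are where loss is greatest. The first goes too far: completeness through t3 still describes treatment and the first month afterwards. The second has no basis, since the article gives only an overall dropout allowance and nothing by visit.

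**On practicality.** The article shows a screening step but confirms no log of patients who were not enrolled. That objection holds and limits the remedy.

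**Conclusion.** There are two separate defects, both worth correcting.

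The recruitment rate as defined is a progress figure. It is 100% whenever 60 are enrolled, 70% at the reported count, and silent on uptake and on accrual per centre per month. The conflicting end dates leave it without a fixed time base. That conclusion rests on the text alone; the screening counts and accrual dates in the calculation are assumptions that show the range.

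The data completeness defect is a mismatch between Table 1 and the rest of the article, not a faulty definition. Its size is about 7.5 percentage points (87.5% against 80%) if the protocol's 20% allowance is spread evenly over the five follow-ups, and about 4 to 11 points for total losses of 10% to 30%. A different pattern of loss would change these figures.

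Neither defect affects the efficacy comparisons. Both affect what the pilot passes on to the larger trial.

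**What to change.** - **Recruitment rate.** In Feasibility Primary Outcomes and Statistical Analysis, define it as (a) randomized per centre per month and (b) randomized over screened, or over eligible where screening records allow, each with a 95% confidence interval. Keep enrolled over target only as a progress figure.
- **End date.** Reconcile 31 August 2025 with December 2025, and state whether the date closes enrolment or follow-up.
- **Data completeness.** Move the tick in Table 1 to t5 and report completeness by arm and visit.

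**Cost.** Rewording in two sections, one reconciled date and one table row. The feasibility outcomes are descriptive with no hypothesis tests, so redefining them during the trial raises no type I error issue. Enrolment dates and centre should already be on record, so (a) should need no new data. For (b), if patients who were not enrolled have not been logged so far, the uptake fraction can be given only from the date logging starts, and the report should state that limit.

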**Methods:**

In this double-center, assessor-blinded, randomized controlled trial, 60 patients with ISSNHL accompanied by tinnitus will be randomly allocated to either the EA group, receiving EA combined with medication, or the control group, receiving standard medication treatment, for a total treatment duration of 4 weeks. Follow-up assessments will be conducted at weeks 2 and 4, and at 1, 2, and 3 months after treatment. The feasibility primary outcomes are recruitment rate, adherence rate, data completeness, and safety outcomes. The primary outcome measures will include pure tone audiometry, tinnitus matching, and the Tinnitus Handicap Inventory, while the secondary outcome measures will comprise speech-recognition thresholds in noise, the Self-Rating Anxiety Scale, and the 36-item Short Form Health Survey Questionnaire.

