## Methods

### Design and Setting

The study is designed as a prospective, single-blinded RCT. It will take place in the clinics of Beijing Tongren Hospital, Capital Medical University, and the Acupuncture and Moxibustion Hospital, China Academy of Chinese Medical Sciences (CACMS). Eligible participants will be randomized in a 1:1 ratio to either the EA group (EA plus medication) or the control group (standard medication alone). This pilot trial will apply a longitudinal follow-up design, with a baseline assessment before enrollment (t–1), allocation and intervention initiation at t0, on-treatment follow-ups at week 2 (t1), week 4 (t2), and posttreatment follow-ups at 1 month (t3), 2 months (t4), and 3 months (t5) after intervention completion, barring loss to follow-up. This trial will be reported in accordance with the CONSORT (Consolidated Standards of Reporting Trials)-EHEALTH (see Multimedia Appendix 1) statement, which defines standard reporting items for RCTs [27]. Participant recruitment began on July 15, 2024, with the study scheduled to continue until December 2025. The flowchart is illustrated in Figure 1, and the overall procedure is presented in Table 1.

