### Oversight and Monitoring

The principal investigators (JH and XH) will oversee the trial and report any serious adverse events to the Tongren Hospital Ethics Committee. Detailed records of adverse events—including their timing, severity, and treatment—will be maintained. In the event of an adverse reaction, a senior acupuncturist and otolaryngologist will evaluate whether the patient should be excluded from the study, and the clinical supervisor will be informed accordingly. Researchers will document the event details in the case report form (CRF; Multimedia Appendix 2) and ensure follow-up care until the patient stabilizes, with a summary report sent to the relevant authorities. Audiologists, acupuncturists, and nurses will conduct weekly follow-up calls to monitor symptoms and manage potential adverse reactions.

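### The primary safety outcome stops at the end of treatment, but Table 1 schedules adverse events to 3 months afterwards, and posttreatment events enter no stated safety summary

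*Protocol article*

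**What the plan says.** The section on Feasibility Primary Outcomes names safety as one of four primary feasibility outcomes and defines it as "recorded as the incidence of adverse events during the treatment period, based on session-by-session reports". The feasibility paragraph of Statistical Analysis gives the same window and source and adds the summary measure: "the incidence of adverse events during the treatment period (safety outcomes, recorded from session-by-session reports and summarized as total events and incidence rate per 100", the unit being person-sessions. It presents these outcomes descriptively.

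Table 1 has a row labelled "Adverse events" under its feasibility outcomes. The row is ticked at t1, t2, t3, t4 and t5. Design and Setting places t1 and t2 at weeks 2 and 4 of treatment, and defines the other three as "posttreatment follow-ups at 1 month (t3), 2 months (t4), and 3 months (t5) after intervention completion". The abstract describes the intervention as given "for a total treatment duration of 4 weeks".

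Oversight and Monitoring requires a record of each event's timing, severity and treatment, provides weekly follow-up calls with no stated end date, and has staff "ensure follow-up care until the patient stabilizes". It does not say how events that begin after treatment are to be summarized.

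**The concern.** The text fixes when a safety event counts, where it is recorded and how it is summarized. All three are tied to the treatment sessions. Table 1 places collection at t3 to t5 under the same group of outcomes, and no sentence gives those later records a use in the safety result.

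Safety is a primary outcome of a pilot meant to inform a larger trial. If the text is followed literally, the primary safety figure covers only events during treatment, and whether posttreatment events appear elsewhere is left to whoever writes the report. If Table 1 is taken as the scope, the figure runs to t5. The choice should be fixed before the data are analyzed. The article reports that analysis is still to come, so there was time to settle it.

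**Working it through.** The article states no figure for this point, so there is none to reproduce. The check is a count of visits and sessions, followed by what the definition does with each kind of event.

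**1. Scheduled visits (Table 1; timing from Design and Setting)**

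| Visit | Timing | Adverse events ticked | Within the treatment period |
|---|---|---|---|
| t1 | week 2 | yes | yes |
| t2 | week 4 | yes | yes |
| t3 | 1 month after treatment | yes | no |
| t4 | 2 months after treatment | yes | no |
| t5 | 3 months after treatment | yes | no |

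Scheduled visits: 5. Within the window: 2. Outside it: 5 − 2 = 3, or 3/5 = 60% of the visits.

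**2. Can the stated rate hold posttreatment events?**

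- The Interventions section prescribes 4 sessions a week for 2 weeks, then 3 a week for 2 weeks: 4 × 2 + 3 × 2 = 14 sessions per electroacupuncture participant, all within the 4 weeks.
- With 30 participants in that arm (Sample Size section), the denominator is at most 30 × 14 = 420 person-sessions.
- After week 4 it grows by 0, and there are no further session reports in which an event could be entered.

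So a posttreatment event has neither a source record nor a denominator under the stated definition.

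**3. Where each kind of event goes**

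- Onset during treatment, noted in a session report: counted.
- Onset during treatment, first noted at a call or visit: inside the window by onset, although the stated source is session reports. Recording of event timing makes the assignment possible.
- Onset after treatment, noted by call or at t3, t4 or t5: outside the window and outside the source. No stated summary receives it.

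**4. Size of the effect on a reported incidence**

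Let *a* be the participants in an arm with at least one on-treatment event, *b* those whose only events are posttreatment, and *n* the number in the arm.

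- On-treatment proportion: *a*/*n*
- Proportion from t0 to t5: (*a* + *b*)/*n*
- Difference: *b*/*n*, which cannot be negative

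With *n* = 30, each such participant adds 1/30 = 3.3 percentage points. With *n* = 25, the number per arm before the dropout allowance, it is 1/25 = 4.0 points. The article gives no basis for *b*, and it may be 0.

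**The case against.** The strongest reply is that this is an ordinary design choice. A primary safety window may be shorter than the collection period, and the two text definitions agree with each other. Table 1 is a schedule of procedures. Its ticks do not generally define outcome windows: adherence covers the 4 weeks of sessions but is ticked only at t3. How events are tabulated by period is often left to the full protocol or the analysis plan.

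Much of this stands. The window is legitimate, and Table 1 alone does not prove that the primary outcome was meant to run to t5. What remains is that the article does not simply stay silent. It fixes window, source and summary in two places, and the adverse-event row has its own five-visit pattern while the other feasibility rows carry a single tick at t3. The later collection is evidently intended, and the stated summary has no room for it.

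Several stronger readings are tempting, and the document does not support them:

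- *The two text definitions give different results.* They use the same window; the mismatch is with Table 1.
- *Effects of the last sessions are first seen at t3.* The weekly calls could detect them sooner, and recorded timing lets an event be dated by onset instead of by visit.
- *A fall in hearing during follow-up would go unreported.* Pure tone audiometry is scheduled at t3, t4 and t5 and is analyzed over all six time points and between groups at each.
- *About three quarters of the time at risk is lost.* Three months of 4 weeks are 12 of 16 weeks, or 75%, but that is a share of calendar follow-up. All electroacupuncture sessions fall in the first 4 weeks, so neither this share nor the 60% of visits estimates missed events.
- *Later events will be suppressed.* They are to be documented, and serious ones go to the ethics committee.

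**Conclusion.** The point holds as a mismatch between a primary outcome definition and the collection schedule. Three of the five scheduled adverse-event visits lie after treatment, and events with onset in that period enter no safety summary the article states. The per-session rate could not take them in, since no sessions occur after week 4.

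This rests on taking the treatment period as the 4 weeks ending at t2, as the abstract and the column headings of Table 1 indicate, and on the article alone. A fuller plan may already contain a posttreatment summary. The number of events concerned is unknown and may be small. The outcome is descriptive, so no test or error rate is affected. It is a worthwhile and cheap improvement to the completeness of the safety result and does not threaten the trial's validity.

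**What to change.** Keep the on-treatment figure as defined. In both Feasibility Primary Outcomes and Statistical Analysis, add the number and proportion of participants with at least one adverse event from t0 to t5, by arm. Assign events by date of onset, and split the display into on-treatment (t0 to t2) and posttreatment (after t2 to t5). State that the source for the added summary includes visit and call records as well as session reports.

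A participant-level proportion also works in the control arm, which has no electroacupuncture sessions to serve as a denominator.

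The cost is a sentence in two places and one extra table. The data are already scheduled for collection. The reported incidence to t5 may be slightly higher than the on-treatment figure; showing both lets the reader see why.
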